## Outcome measures

4

Baseline and postintervention measurements corresponded with the beginning and the end of the school year (September 2017 and June 2018, respectively). Table 2 summarizes the variables measured.

**Table 2 T2:**
[figure not shown]
Study variables.

The measurements were made at school by evaluators who were previously trained to standardize the measurements and blinded to the group in which participants were allocated.

### Primary outcome

4.1

*Anthropometric variables* were measured twice, and their average was considered for the analyses. Weight was measured using a scale (Seca 861) with the child in light clothing and barefoot. For height, a wall stadiometer (Seca 222) was used with children barefoot and upright while the sagittal midline touched the backboard. Children had to look straight ahead, and the line of sight had to be parallel to the floor.

*Body composition.* Body mass index (BMI) was calculated as weight (kg)/height (m)^2^. Waist circumference was considered as the mean of 3 measurements using a flexible tape at the midpoint between the last rib and the iliac crest at the end of a normal expiration. The percentage of body fat and fat-free mass were measured by using an 8-electrode Tanita Segmental-418 bioimpedance analysis system (Tanita Corp., Tokyo, Japan).^[24]^ Body fat and fat-free determinations were performed under controlled temperature and humidity conditions. In addition, the measurements were done before breakfast, after urination, and after a 15-minute resting period.

*Blood pressure.* Systolic and diastolic blood pressure and heart rate were measured in a quiet place and after a 5-minute resting period using an OMRON-M5-I device (Omron Healthcare UK Ltd.),^[25]^ and cuff size was used according to the child's arm circumference. We considered for analyses the mean of the 2 measures separated by 5 minutes each.

*Biochemical determinations.* Blood samples were drawn from the cubital vein between 9.00 and 10.00 am, and after a 12-hour fasting period. Two aliquots from each sample were frozen for future determinations that could be of interest for parents.

*Lipid profile.* Cholesterol, triglycerides, high-density lipoprotein cholesterol (cHDL) and low-density lipoprotein cholesterol (cLDL), glucose, apolipoproteins A1 and A2, insulin, glycated hemoglobin A1c (HbA1c), C-reactive protein, and brain-derived neurotrophic factor (BDNF) were determined. FPG and lipid profile measurements were performed using the Cobas 8000 Roche Diagnostics system. Insulin was determined with the Architect i2000 Abbot Diagnostic system. C-reactive protein was measured using the Cobas 6000 Roche Diagnostic system and HbA1c by high-performance liquid chromatography (HPLC) with the analyzer ADAMS HA 8180 V Menarini Diagnostic, which was standardized for the Diabetes Control and Complications Trial (DCCT), and the International Federation of Clinical Chemistry and Laboratory Medicine (IFCC). Samples were refrigerated when they were drawn farther than 75 minutes away from the laboratory. Finally, biochemical determinations allowed for estimating insulin resistance using the HOMA model and determining the metabolic syndrome index.^[26]^

*Physical fitness parameters* were measured after a 4-minute warm-up, using the PREFIT battery^[27,28]^ as follows:

–*Cardiorespiratory fitness* was measured using the Course Navette test (20-m shuttle run test). Two lines 20-m apart were painted on the floor. Children were encouraged to run back and forward following the sound signal of a prerecorded tape. This sound started with a cadence of 6.5 km/h and increased in 0.5 km/h each minute. Children failed the test when they did not reach the lines before the signal sounded twice. Maximal oxygen intake was calculated by applying the preschool-adapted 20-m shuttle-run (PREFIT) formula.^[29]^–*Muscle strength* was assessed based on upper body and lower explosive body strength.

A digital dynamometer with adjustable grip TKK 5401 Grip-DW (Takeya, Tokyo, Japan) was used to measure upper body strength in kilogram. The test was performed twice with the right hand and twice with the left hand; the mean average of the 4 measurements was calculated.

The standing long jump was used to measure lower explosive body strength. Children stood behind a line with their feet approximately shoulder width apart and jumped as far as possible with both feet. The test measures the distance in centimeters from the starting line to the back of the children's heels. The best of 3 trials was recorded.

–*Speed ability* was assessed using the speed–agility test 4 × 10 shuttle run test. Children ran as fast as they could 4 times between 2 lines 10-m apart. The best of 2 trials in a 5-minute interval was recorded in seconds. For analyses, this variable was multiplied by −1, as less time represents better results.–*Flexibility* was measured by the sit-and-reach test. Children sat on the floor with their legs out straight ahead and feet placed flat against a box. The maximum distance the children could reach with their fingertips by flexing the trunk keeping the fingers level and without flexing the knees was measured. The best mark from 3 attempts was used for analyses.^[30]^

### Co-primary outcomes

4.2

#### Executive functions

4.2.1

The 3 core executive functions ^[31]^ (i.e., inhibition, working memory, and cognitive flexibility) were measured by using the NIH tool box.^[32]^ All measurements were performed using the digital format test, and was administered to the children individually and in a quiet room.

In brief, inhibition was measured using an adapted version of the Eriksen Flanker Task.^[33]^ The version included a practice block of 4 trials that children passed if they got ≥3 trials. If so, a 20-trials block is presented consisting of a pseudorandom sequence of congruent and incongruent trials. Validation procedures previously reported were used to calculate accuracy percentage, and reaction time on congruent and incongruent trials; in addition, raw scores were obtained.^[34]^

Working memory was measured using the List Sorting Working Memory Test.^[34]^ Children were presented a series of illustrated pictures, after that they were asked to verbally repeat the names of the pictures in order of size, from smallest to largest. The number of objects in the series increased by one each time. Two list versions were presented, the first presenting items in one category (i.e., animals), and the second presenting items in 2 categories (i.e., animals and food). In the second version, children were asked to remember and organize items by category and size.

Cognitive flexibility was measured using the Dimensional Change Card Sort test.^[33]^ This tool presented a stimulus by “color” or “shape,” and children were asked to adapt their response according to the relevant dimension. First, a 4-trial practice block was presented, from which children needed to pass 3 to get the mixed 30-trial block. During the mixed block, “color” and “shape” trials were presented in a pseudorandom order. Validation procedures previously reported were used to calculate accuracy percentage and reaction time on pre-switch and post-switch trials; in addition, raw scores were obtained.^[33]^

*Academic achievement* was assessed through school records on language and mathematics academic subjects. Scores at the end of the 2016 to 2017 and the 2017 to 2018 school years were considered as baseline and final measurements, respectively.

*Physical activity.* In a subsample of 500 randomly selected children, physical activity was objectively measured using GENEActive accelerometers (ActivInsights) for 7 consecutive days (including nights), with a fixed frequency of 30.0 Hz to collect raw acceleration data measured in “g” for each movement axis (*x*, *y*, and *z*), to measure the physical activity of children in the IG and the CG. Data were stored directly in the memory of the device and expressed in units of milligram (1000 mg = 1 g = 9.81 m/s^2^).^[35]^ We considered as valid measurements those of ≥5 days, including 1 weekend day.

*Health-related quality of life* was measured using the validated Castilian version of KIDSCREEN-27.^[36]^ Children and parents were asked to separately complete this questionnaire to compare results.

*Motor competences* were assessed using 5 tests that evaluate gross motor skills (2 for ‘aiming and catching’ and 3 for ‘static and dynamic balance’) of the Movement Assessment Battery for Children for children from 7 to 10 years old. ^[37]^

### Confounding variables

4.3

The following were considered as confounding variables:

Food consumption was estimated using the Children's Eating Habits Questionnaire (CEHQ)^[38]^ completed by parents.Family socioeconomic status was estimated using the Spanish Epidemiology Society Scale. Mothers and fathers reported their respective educational levels and employment status, and an index was calculated considering both.^[39]^Parents reported sexual maturation identifying their children's pubertal status on figures based on the Tanner stages.^[40,41]^Birth weight, breastfeeding, gestational age, and parents’ information (weight and height) were also collected.

## Data analysis and management

5

### Sample size

5.1

The sample size was estimated by considering a 0.3 difference mean change between the IG and the CG in cardiorespiratory fitness, as has been reported in previous studies.^[42]^ The estimates were calculated considering an alpha error of 0.05 and statistical power of 0.80. In addition, a mean of 40 children was considered in each classroom with a 15% dropout rate. For sample size calculation, optimal design software was used and Donner and Klar's models were considered.^[43]^

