### Recruitment and allocation

3.2

The Clinical Research Ethics Committee of the ‘Virgen de la Luz’ Hospital in Cuenca approved the study protocol. The development of this project was supported by the Department of Education and Science of the Junta de Communities of Castilla-La Mancha (Spain), which sent a letter informing each school that agreed to participate about the study. After that MOVI-daFIT! researchers provided information about the objectives and methods of the study to the head teacher, the school board, and the physical education teachers of the schools. The consent of the School Council, board of community participating in school management, was required to participate in MOVI-daFIT!. Finally, 10 schools from 10 towns in the province in Cuenca, Spain, agreed to participate (Fig. 1).

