**Figure 1 F1:**
[figure not shown]
Flow chart of trial participants. CG = control group; IG = intervention group.

After approval from School Councils, the schools were randomly assigned to either the intervention group (IG) or the control group (CG), by using the statistical package StatsDirect.

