### Inclusion and exclusion criteria

3.4

To participate in the study, schools were required to have at least one full classroom of fourth grade and another of fifth grade. Children were excluded when presenting Spanish learning difficulties; teachers or parents reported any child's serious physical or mental disorders which could impede participation in the activities of the program; or pediatricians reported any child's chronic disorder such as heart disease, diabetes, or asthma that could prevent participation in the activities of the program.

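### The 80% power in section 5.1 rests on a group size given per classroom, but 10 schools were randomised; at school level it holds only for a small, unstated ICC.

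*Protocol article*

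**What the plan says.** Section 5.1 (Sample size) plans for a difference in one outcome, "considering a 0.3 difference mean change between the IG and the CG in cardiorespiratory fitness", with "an alpha error of 0.05 and statistical power of 0.80". The group size and loss are given as "a mean of 40 children was considered in each classroom with a 15% dropout rate". On method it says that "optimal design software was used and Donner and Klar's models were considered". It gives no ICC, number of clusters or total sample size, and no unit or SD for the 0.3.

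Other sections fix the level at which the trial works. Under section 3.2, schools were allocated at random after their School Councils approved, and "10 schools from 10 towns in the province in Cuenca, Spain, agreed to participate". Section 3.4 requires each school to have "at least one full classroom of fourth grade and another of fifth grade", so every school contributes at least two classrooms. Section 5.2 names school as the cluster in the mixed models, which also adjust for baseline.

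**The concern.** In a cluster trial, power depends mainly on the number of randomised units and on how alike children are within a unit. The one size entered in section 5.1 belongs to a unit that was not randomised and is not the analysis cluster. The 10 schools appear as the number that agreed to join, and nothing in the article links that number to the calculation.

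This matters when the result is read. Against a stated 80% power, a null finding suggests that an effect of 0.3 is unlikely. If the 10-school design had much less power, the same finding would say little about whether the programme works.

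**Working it through.** **Inputs from the article.** Difference 0.3; alpha 0.05; power 0.80; 40 children per classroom; 15% dropout (section 5.1). 10 schools (section 3.2). At least two classrooms per school (section 3.4).

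**Assumptions.** 0.3 is in SD units; the split is 5 versus 5; the test is two-sided; each school has two classrooms unless stated otherwise. The ICC is varied because none is given.

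**Step 1: can the 0.80 be reproduced?** Not uniquely, because the ICC and the number of clusters are missing. Several routes lead to it:
- Ignoring clustering: n per arm = 2(1.96 + 0.84)² / 0.3², which rounds up to 175, or 175 / 0.85 = 206 recruited per arm.
- Treating 20 classrooms of 40 × 0.85 = 34 as independent clusters (18 df): 80% holds up to an ICC of about 0.023.
- Using 10 schools of 68: 80% needs an ICC of about 0.007 (step 3).

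The article does not say which route, if any, was taken.

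**Step 2: power at school level.** Children analysed per school: m = 2 × 40 × 0.85 = 68. Schools per arm: k = 5.

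SE of the difference, in SD units = √{2[1 + (m − 1)ICC] / (k m)}; power from the noncentral t with 2k − 2 = 8 df (critical value 2.306) and noncentrality 0.3 / SE.

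| School ICC | 1 + 67 × ICC | SE | 0.3 / SE | Power (t, 8 df) | Power (normal) |
|---|---|---|---|---|---|
| 0 | 1.00 | 0.077 | 3.91 | 93% | 97% |
| 0.01 | 1.67 | 0.099 | 3.03 | 76% | 86% |
| 0.02 | 2.34 | 0.117 | 2.56 | 61% | 72% |
| 0.05 | 4.35 | 0.160 | 1.88 | 38% | 47% |

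**Step 3: largest ICC at which power is still 80%, and power at ICC 0.05.**

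| Case | Limit (t) | Limit (normal) | Power at 0.05 (t / normal) |
|---|---|---|---|
| Two classrooms, m = 68 | 0.007 | 0.014 | 38% / 47% |
| Three classrooms, m = 102 | 0.012 | 0.019 | 40% / 49% |
| Four classrooms, m = 136 | 0.015 | 0.021 | 42% / 51% |
| m = 68, baseline r = 0.7, 0.3 in unadjusted SD | 0.029 | 0.042 | 64% / 75% |

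The last row multiplies the variance by 1 − 0.7² = 0.51, so the effective difference is 0.3 / √0.51 = 0.42. Without baseline adjustment, even an unlimited number of children per school lifts the limit only to 0.022 (t) or 0.029 (normal). The number of schools is the constraint.

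**Step 4: detectable difference at 80% power** (m = 68, 8 df, no baseline adjustment): the noncentrality needed is 3.20, so the difference is 3.20 × SE. That gives 0.32, 0.38 and 0.51 SD at ICC 0.01, 0.02 and 0.05.

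**The case against.** The article names cluster-trial software and methods and never says that the classroom was the cluster. Forty per classroom may simply be the figure from which a school size was built. This stands: a reader might infer that power was worked out with classrooms as independent clusters, but the text does not show it. It shows only that the one size reported is not at the randomised level.

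The ICC is entirely assumed, and a condensed article may leave it, the cluster count and the total to the full protocol. That also stands, so their absence alone is not the point. The point is that the power figure is printed beside an input at another level than the randomisation and the analysis.

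The limit of 0.007 is sensitive. Two classrooms is the minimum, and the planned baseline adjustment could help considerably: with r = 0.7, power is 96% and 88% at ICC 0.01 and 0.02. The unit of 0.3 matters as well. With 68 per school and 8 df, the limit would be 0.025 for a standardised difference of 0.4 and 0.047 for 0.5, but only 0.0006 for 0.25. A flat statement that power fails above 0.007 is therefore not supported.

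A reader might also take 40 as the total per school, which would make the shortfall worse. The article does not support that: it requires two classrooms per school, and the accelerometer subsample of 500 children (section 4.2.1) exceeds 10 × 40 = 400.

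**Conclusion.** The concern holds in conditional form. The mismatch of level is on the page, and the 80% cannot be verified from what is stated. If 0.3 is in SD units and the split is 5 versus 5, the claim needs a school ICC below about 0.007 in the two-classroom case with 8 df. The limit is about 0.014 by normal approximation, 0.012 to 0.015 (t) with three or four classrooms, and about 0.03 (t) to 0.04 (normal) with baseline adjustment at r = 0.7 and 0.3 in unadjusted SD. At ICC 0.05 power is below 80% in all of these cases.

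A reader might conclude that the trial is shown to be underpowered. The documents do not support that, since they give neither the ICC nor the scale of the 0.3. What they support is that an unqualified 0.80 should not stand for this design.

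**What to change.** Redo section 5.1 with the school as the cluster. State the number of schools per arm, the expected number of children analysed per school, the ICC used in planning (or that none was used), and the unit and SD of the 0.3, including whether it refers to baseline-adjusted change.

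In place of the unqualified 0.80, report school-level power and detectable difference over an ICC range, for example 0.01 to 0.05, labelled as an assumption. If baseline adjustment is credited, give the assumed correlation. Add that a null result will be interpreted by its confidence interval and not by the planned power.

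The cost is one recalculation and a rewritten paragraph. No extra schools are needed and the planned analysis does not change, but the stated power will look less favourable.

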### Analyses of outcomes

5.2

After measurements, participants’ data will be entered into a database by 2 independent researchers. Blinding on handling data will be assured by separating measurements values from general participant's information. Statistical analyses will be performed in 3 waves. First, the effectiveness of the randomization processes will be checked by exploring outlier values, and the normal distribution of the variables using the Kolmogorov Smirnov test and graphical procedures (normal distribution plots). After checking the truthfulness of outliers and extreme values, these will be winsorized using the 1st percentile and 99th percentile of the distribution of variables. Before conducting the analyses, and after considering the missing at random or missing completely at random nature, children with missing data will be imputed using chained equations.

Second, mixed regression models^[44]^ will be used to assess the change between the baseline and final variable measurements. For these analyses, each variable will be considered as an independent variable, and the intervention as a fixed effect. In addition, the analyses will be adjusted for baseline data, age, sex, and school (cluster).

Finally, the previous analyses will be done using propensity score methods for comparing the IG and the CG in the scenario in which IG subjects have the same characteristics as the CG ones at the baseline. This statistical method allows each child in the IG to be matched with a child in the CG, by using a variable as reference.

Results will be considered statistically significant at *P* < 0.05. The analyses will be performed using version 9.2 of STATA14. Finally, statisticians conducting the analyses will be blinded to the participant's allocation.

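### The model in section 5.2 misnames the outcome and leaves the role of school open; with ten schools and large-sample tests, the 5% level would not hold

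*Protocol article*

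**What the plan says.** Section 5.2 of the protocol article (Analyses of outcomes) describes one model for all outcomes. Mixed regression models "will be used to assess the change between the baseline and final variable measurements". On the roles of the terms it says that "each variable will be considered as an independent variable, and the intervention as a fixed effect". On covariates it says that "the analyses will be adjusted for baseline data, age, sex, and school (cluster"), so the only mention of school is as the last item of the adjustment list, tagged as the cluster. No random effect, estimator, reference distribution or degrees-of-freedom method is named. The decision rule is short: "Results will be considered statistically significant at" P < 0.05. On software: "The analyses will be performed using version 9.2 of STATA14".

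Section 3.2 fixes the design that the model must fit: "10 schools from 10 towns in the province in Cuenca, Spain, agreed to participate", and "the schools were randomly assigned to either the intervention group (IG) or the control group (CG").

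**The concern.** Three things in this short paragraph bear on the arm comparison.

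- The measured variable is put on the wrong side of the regression. Each outcome should be the dependent variable.
- School appears among covariates that are ordinarily fixed effects. Each school lies wholly in one arm, so a set of fixed school terms would absorb the arm contrast.
- If school is a random effect, the precision of the arm effect rests on ten school-level units. A test that treats ten units as a large sample understates the uncertainty. Because the same model serves every outcome, so would the same problem.

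At stake are whether the analysis can be reproduced from its description, and whether a nominal 5% test is a 5% test.

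**Working it through.** **Inputs from the article.** Ten schools, randomised whole (section 3.2); P < 0.05 (section 5.2); a mean of 40 children per classroom and 15% dropout (section 5.1); at least one classroom in each of two grades per school (section 3.4). Retained children per school are therefore 40 × 0.85 = 34 with one classroom's worth, or 2 × 34 = 68 with two.

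**Assumptions not in the article.** Five schools per arm, two-sided tests, equal school sizes, no covariates in the simulation, and an intraclass correlation (ICC) of 0 to 0.10. The article states no ICC. The relevant ICC is the one left after adjustment for baseline, age and sex.

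**1. School as a fixed covariate.** Intercept, arm and nine school indicators make 11 columns. The design matrix has rank 10, so the arm effect is not identified.

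**2. School as a random intercept.** Take y_ij = β0 + β1·arm_j + u_j + e_ij for child i in school j. The arm effect is estimable, and the between-school information has 10 − 2 = 8 degrees of freedom. The 97.5% point of t on 8 df is 2.31, against 1.96 for the normal; 2.31/1.96 = 1.18.

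**3. Size of a z test, between-school variance clearly positive.**
- REML: P(|t8| > 1.96) = 8.6%.
- Maximum likelihood (ML) divides the between-school sum of squares by 10 instead of 8. The effective cut-off is 1.96 × √(8/10) = 1.75, and P(|t8| > 1.75) = 11.8%.

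**4. Simulation under no effect.** 40,000 trials per row, variance estimate held at or above zero. The Monte Carlo standard error near 5% is √(0.05 × 0.95/40,000) = 0.1 percentage points.

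| Children per school | ICC | ML, z | REML, z | REML, t 8 df | School means, t 8 df |
|---|---|---|---|---|---|
| 34 | 0 | 4.3% | 3.8% | 1.5% | 5.0% |
| 34 | 0.01 | 6.9% | 5.7% | 2.7% | 4.9% |
| 34 | 0.02 | 8.5% | 6.6% | 3.5% | 4.9% |
| 34 | 0.05 | 11.1% | 8.2% | 4.6% | 5.0% |
| 34 | 0.10 | 11.8% | 8.6% | 5.2% | 5.2% |
| 68 | 0 | 4.3% | 3.8% | 1.5% | 5.1% |
| 68 | 0.01 | 8.8% | 6.9% | 3.6% | 5.1% |
| 68 | 0.02 | 10.6% | 8.0% | 4.4% | 5.1% |
| 68 | 0.05 | 11.7% | 8.6% | 4.9% | 5.0% |
| 68 | 0.10 | 12.0% | 8.9% | 5.1% | 5.1% |

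The article's only figure to reproduce here is the nominal 5%. The school-means t test reproduces it in every row (4.9% to 5.2%). Both z columns exceed it from ICC 0.01 upward and neither does at ICC 0. Changing the reference distribution without changing the estimator is not enough: at ICC 0.10, ML with t on 8 df still gives 7.3% (34 children) and 7.5% (68).

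**The case against.** The article can be read more favourably, and much of that reading stands.

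- **Reversed regression.** A reader might infer that the outcome will really be fitted as a predictor. The same paragraph makes the intervention a fixed effect and says the models assess change from baseline. The measured variable can then only be the response. This is a wrong word, and no estimate would change because of it.
- **Not estimable.** A reader might infer that the arm effect cannot be estimated. That needs school to be a fixed covariate, the reading that fits least well: the models are called mixed, school is tagged as the cluster, and section 3.1 declares a cluster trial to be conducted and reported under the CONSORT cluster extension. What remains is an ambiguity about the central term of a cluster-trial model.
- **Error certainly above 5%.** A reader might infer, because Stata is named, that its default test will be used and will exceed 5%. The article names no command, estimator or reference distribution, and these may sit in an analysis plan not shown. The figures above are conditional on a z test and on the ICC.
- **Imputation without school.** The article says only that "children with missing data will be imputed using chained equations". It does not say that school is left out of the imputation model, so no error can be charged there.

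The objection does not remove the combination that the article does fix: a mixed model, ten randomised schools and a 5% criterion, with nothing to show that the small number of schools was taken into account in the test.

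**Conclusion.** The point holds in a limited form. There is one misstatement (the outcome called an independent variable), one ambiguity (school listed as an adjustment without being named a random effect), and one conditional weakness. If the natural random-intercept model is tested with large-sample z statistics, type I error is about 7% to 12% under ML and 6% to 9% under REML for ICCs of 0.01 to 0.10, with no excess at ICC 0. The size for any one outcome depends on its own ICC after adjustment, so the inflation should not be taken as equal across outcomes. The result also rests on the assumed five-by-five split, equal school sizes and two-sided tests. The text should be corrected and a small-sample method stated; the article does not show that an invalid test was chosen.

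**What to change.** Reword the model paragraph in section 5.2 along these lines: each final measurement is the dependent variable; arm, baseline value, age and sex are fixed effects; school is a random intercept; models are fitted by REML, and the arm effect is tested with a small-sample degrees-of-freedom correction such as Kenward-Roger. A school-level t analysis on 8 df, using school means of covariate-adjusted residuals, serves the same purpose. The two need not agree exactly when school sizes differ or the variance estimate is zero, so one should be named in advance. The software version should be stated unambiguously at the same time, so that the chosen option can be checked as available.

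The cost is one paragraph and an analysis setting; conduct and data collection are unaffected. Intervals become about 18% wider than with REML and z. Against ML and z the factor is 1.18 × √(10/8) = 1.32, where the between-school variance is estimated above zero. REML with t on 8 df is also conservative at low ICC: 1.5% at ICC 0, and 3.5% to 4.4% at ICC 0.02. The school-means t test avoids that conservatism in the balanced case simulated.

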### Design

3.1

This study was designed as a cluster randomized controlled trial with 2 parallel groups. The CONSORT 2010 statement: extension for cluster trials^[22]^ will be used to conduct and report results of this trial.

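### Every outcome is re-analysed after pairing individual children on one variable in a school-randomised trial, and the plan does not say which of the two results decides

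*Protocol article*

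**What the plan says.** The Design section (3.1) states: "This study was designed as a cluster randomized controlled trial with 2 parallel groups". Section 3.2 reports that "10 schools from 10 towns in the province in Cuenca, Spain, agreed to participate", and the text after Figure 1 makes the school the unit of allocation.

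Section 5.2, Analyses of outcomes, describes three waves:

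- The first covers data checks, winsorizing and imputation.
- The second fits mixed regression models to change from baseline, with the intervention as a fixed effect and adjustment for baseline value, age, sex and school.
- In the third, "the previous analyses will be done using propensity score methods for comparing the IG and the CG". The aim is a comparison in which intervention children share the control children's baseline characteristics. The method is then explained: "This statistical method allows each child in the IG to be matched with a child in the CG, by using a variable as reference".

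One significance threshold, P < 0.05, follows for all results. Neither the second nor the third wave is called primary, supportive or exploratory.

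Section 4.3 introduces a separate list with "The following were considered as confounding variables". It includes family socioeconomic status and pubertal status. Neither is named in the second-wave model.

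**The concern.** Three things are fixed badly here.

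**The unit of matching.** Allocation was by school, so chance imbalance between arms arises largely between the 10 schools. Pairing a child in one school with a child in another does not change how the schools themselves differ.

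**The stated method does not reach the stated aim.** Matching on one variable aligns that variable and leaves the other baseline characteristics as they were. A propensity score normally combines several covariates, so the sentence naming propensity methods and the sentence describing the matching do not obviously describe the same procedure.

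**Two answers per outcome.** The third wave repeats the second for every outcome, at the same threshold and without a ranking. If the two disagree, the plan gives no ground for preferring one, and that freedom recurs for each outcome in section 4. The matched result may also describe a subset of children chosen by the matching rather than everyone in the randomised schools.

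**Working it through.** The plan gives no figure to reproduce for the matching step, and section 5.1 states no intracluster correlation (ICC). The numbers below illustrate size under stated assumptions.

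**1. Two unranked tests per outcome**

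Inputs: threshold 0.05 for each analysis (section 5.2), taken as two-sided (critical value 1.96) because sidedness is not stated. The correlation r between the two test statistics is assumed, because the plan gives no basis for it.

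Formula: P(at least one significant) = 1 − P(|Z1| < 1.96 and |Z2| < 1.96), with Z1 and Z2 bivariate normal with correlation r.

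- Independent tests (upper limit): 1 − 0.95 × 0.95 = 0.0975.
- r = 0.7: 0.084.
- r = 0.9: 0.070.
- r = 0.95: 0.064.
- One designated analysis: 0.05.

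The correlated cases come from 1,000,000 simulated pairs. The two analyses share most of their data, so the higher correlations are the more plausible. The excess over 0.05 is then 0.014 to 0.034 per outcome for r from 0.95 to 0.7.

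**2. Children lost, and the role of school**

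Inputs: 10 schools (section 3.2). Assumed: 5 schools per arm, 40 children per school (400 in all), no intervention effect, and ICC of 0, 0.01, 0.05 or 0.10. Section 5.1 gives 40 as a mean per classroom; its use as the school size here is an assumption.

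Method: a logistic propensity score on baseline value, age and sex; one-to-one nearest-neighbour matching without replacement; caliper 0.2 SD of the linear score; 1,000 runs per ICC. When school is kept, covariate-adjusted school means are compared by a t test. When it is ignored, matched pairs are compared by a paired t test. For a true rate of 0.05 the simulation standard error is √(0.05 × 0.95 / 1000) = 0.007.

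| Assumed ICC | Share of children dropped | Type I error, unmatched, school kept | Type I error, matched, school kept | Type I error, matched, school ignored |
|---|---|---|---|---|
| 0 | 0.118 | 0.037 | 0.039 | 0.025 |
| 0.01 | 0.119 | 0.047 | 0.054 | 0.049 |
| 0.05 | 0.128 | 0.053 | 0.047 | 0.175 |
| 0.10 | 0.136 | 0.045 | 0.048 | 0.307 |

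Of 400 children, 0.118 × 400 = 47 to 0.136 × 400 = 54 are lost. With school kept, matching leaves the error rate near nominal. The inflation in the last column arises only when school is removed.

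**3. Does single-variable matching meet the aim?**

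This needs no arithmetic. The aim concerns baseline characteristics in general; the method uses one variable, so balance on the rest is left to chance. School-level features are outside it altogether. Nor could school identity be put into the score, because every school lies wholly in one arm: identity would predict arm perfectly and leave no comparable children to match.

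**The case against.** The strongest reply is that the third wave repeats the earlier analyses, and those carry this adjustment: "the analyses will be adjusted for baseline data, age, sex, and school (cluster"). A reader might infer from child-level pairing that the school randomisation is ignored and that type I error is badly inflated. The document does not support that. The natural reading carries the school term over, and with school kept the simulated error is 0.039 to 0.054. The larger values in the table belong to an analysis that the text does not announce.

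A reader might also take it as stated that children are discarded. It is not: the text speaks of matching each intervention child and mentions neither a caliper nor an exclusion. Loss is a likely result of one-to-one matching without replacement. Matching with replacement, or weighting, would lose fewer intervention children or none.

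A third tempting reading is that random allocation leaves no child-level selection to adjust for. That is not shown. Sections 3.2 and 3.3 do not say whether parental consent came before or after allocation, and section 3.5.1 counts a child as having received the intervention only at 80% attendance or more. Checking robustness to baseline imbalance is therefore a legitimate purpose. What is in question is the tool.

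The single variable may be the propensity score itself, loosely worded. If so, matching could balance the child-level covariates in the score, and the complaint about the aim weakens. School-level features would still be untouched, and the two results would still be unranked. The covariate list and matching algorithm could fairly be left to an analysis plan and are not criticised here.

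Finally, adding covariates to the mixed model does not remove unmeasured differences between schools either. That is true. A random school effect does, however, carry those differences into the standard error, and the model keeps every child.

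**Conclusion.** The concern holds in a limited form. The plan commits to a second, child-matched analysis of every outcome in a trial that randomised schools. As described, one-variable matching cannot deliver equal baseline characteristics and does not balance schools. With no ranking at a shared P < 0.05, the chance of a false positive per outcome rises from 0.05 to about 0.064 to 0.084 for assumed correlations of 0.95 to 0.7, and cannot exceed 0.0975 under the bivariate normal model. A loss of about 12% to 14% of children is likely only if matching is one-to-one without replacement, and that figure depends on the simulated caliper and on three matching covariates rather than one.

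The school split, school size, ICC, two-sided testing and the correlation between analyses are all assumptions. The correlation was not estimated from a simulated trial. Further inflation from ignoring school is a conditional risk, not a feature of the plan. The second-wave model is sound in principle; the weakness is that the third wave can compete with it.

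**What to change.** In section 5.2, state that conclusions for each outcome rest on the mixed model with school as a random effect, fitted in all randomised children.

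Replace the matching step with one sensitivity analysis: the same model with prespecified baseline covariates from section 4.3 added, namely the socioeconomic index and pubertal status. This serves the stated purpose of allowing for baseline differences on measured characteristics, keeps all children, and leaves one designated answer per outcome.

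If matching is kept, label it exploratory, keep the school term in it, and say what the matching variable is and how unmatched children are handled.

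The change is to wording only and needs no new data, since both covariates are already collected. The price is that the matched table is lost or moved to exploratory status.
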